## Abstract

**Background:**

The prevalence of otitis media in Greenlandic children is one of the highest in the world. International studies have shown that otitis-prone children may benefit from tubulation of the tympanic membrane. However, it is unknown whether these results can be applied to Greenlandic children and trials on the effects of ventilation tubes in high-risk populations have, to our knowledge, never been conducted.

**Methods:**

The trial is an investigator-initiated, multicentre, randomized, blinded superiority trial of bilateral ventilation tube insertion versus treatment as usual (no tube) in Greenlandic children aged 9–36 months with chronic otitis media with effusion or recurrent acute otitis media. With randomization stratified by otitis media subtype and trial site, a type 1 error of 5% and a power of 80%, a total of 230 participants are needed to detect a decrease of two visits to a health clinic during 2 years, which is considered the minimal clinical relevant difference. The primary outcome measure will be assessed blindly by investigating medical records. Secondary outcome measures are number of episodes of acute otitis media, quality of life, number of episodes of antibiotics administration and proportion of children with tympanic membrane perforations.

**Discussion:**

This trial will provide evidence-based knowledge of the effects of ventilation tubes in children with middle ear infections from the high-risk Greenlandic population. Furthermore, this trial will improve the understanding of conducting randomized clinical trials in remote areas, where management of logistical aspects is particularly challenging.

**Trial registration:**

ClinicalTrials.gov, NCT02490332. Registered on 14 February 2016.

**Electronic supplementary material:**

The online version of this article (doi:10.1186/s13063-016-1770-x) contains supplementary material, which is available to authorized users.

## Background

Otitis media is one of the most common reasons for children to contact health clinics and insertion of ventilation tubes in the tympanic membrane remains the most frequent type of paediatric surgery in the USA as well as the main reason for prescription of out-of-hospital antibiotics to paediatric patients [1–3]. The worldwide socioeconomic consequences of the disease are substantial, owing to treatment and management of the disease and parental absence from work [4].

The prevalence of otitis media and other acute respiratory tract infections in Greenlandic children is one of the highest in the world; 20% of schoolchildren have impaired hearing in the frequencies of normal speech [5–10]. This pattern is also seen in, for example, the indigenous population in Australia [11]. Many theories have been suggested to explain the high prevalence in certain indigenous populations, such as anatomical features, poverty or limited access to health-care, as well as a high bacterial load in the nasopharynx [12–15]. Studies have shown that the prevalence of chronic suppurative otitis media in the two largest towns in Greenland, Nuuk and Sisimiut, is 9% to 14%, which is a public health problem requiring urgent attention, according to the World Health Organization [6, 7, 12]. A total of 91% of children with chronic suppurative otitis media develop permanent hearing loss, which underlines the importance of treatment and management of the disease [9].

Previous studies have shown that risk factors for the development of chronic suppurative otitis media are associated with the number of upper respiratory tract infections, as well as attendance of day care, mothers’ educational status, passive smoking and socioeconomic factors, similar to known risk factors for acute otitis media found in other studies worldwide [7, 8, 10, 16]. It has been suggested that children with chronic otitis media with effusion, as well as recurrent acute otitis media, are more prone to develop chronic suppurative otitis media, and treatment of these conditions might therefore decrease the number of children with chronic suppurative otitis media [6, 17]. The cumulative incidence of chronic suppurative otitis media in Greenland is 14% at the age of 4, with the highest hazard rate between 6 and 12 months [7]. This indicates that the disease develops early in childhood, and calls for intervention as early as possible in otitis-prone children, to limit progression to chronic perforations.

Ventilation tubes are inserted in the tympanic membrane to equalize pressure and allow drainage of middle ear fluid.

According to guidelines from the UK, the USA and Denmark [1, 3, 18–21], there are two indications for the insertion of ventilation tubes in children:Chronic otitis media with effusion and hearing lossRecurrent acute otitis media

Chronic otitis media with effusion is defined as fluid in the middle ear cavity lasting ≥3 months. Recurrent acute otitis media is defined as ≥3 episodes of acute otitis media within 6 months or ≥4 episodes of acute otitis media within 12 months [21].

Guidelines on the treatment of otitis media with effusion are fairly similar and have been recently updated in both the USA and the UK [3, 20]. However, guidelines on treatment of recurrent acute otitis media vary and different guidelines currently exist in the USA, while there are no national guidelines in the UK [1, 19, 21]. This might explain part of the observed international differences in the number of ventilation tube insertions for recurrent acute otitis media [22].

The mentioned international guidelines on treatment with ventilation tubes are generally based on evidence of low methodological quality concerning such outcomes as number of otitis media episodes after treatment, quality of life after treatment, reduction in chronic tympanic membrane perforations after treatment and number of episodes of aural discharge after treatment, according to the GRADE evaluation of quality of evidence [18, 21, 23, 24]. Furthermore, it is primarily children from Western trial populations, and not children from high-risk otitis-prone populations, such as the Inuit in Greenland, who have been randomized in the previous trials. Currently, there are no national guidelines or programmes to ensure prevention and treatment of otitis media and impaired hearing in Greenland. The Greenlandic Ministry of Health has considered introducing ventilation tube insertion as a more consistent treatment modality in order to decrease the burden of otitis media in the country. However, trials on the effects of ventilation tubes among children in high-risk populations have, to our knowledge, never been conducted. We therefore argue that it is both medically and ethically necessary to conduct a randomized clinical trial before ventilation tubes are made part of the routine treatment of children with chronic otitis media with effusion and recurrent acute otitis media in Greenland. Moreover, ventilation tube treatment is currently not a part of standard care in Greenland and this provides a unique opportunity to investigate the unbiased effect of the treatment, which would not be possible in populations where ventilation tube treatment is already standard treatment.

## Methods/Design

### Objective and hypothesis

The primary objective of the trial will be to assess the effects of bilateral insertion of ventilation tubes versus ‘treatment as usual’ with no ventilation tubes in children 9–36 months old with chronic otitis media with effusion or recurrent acute otitis media in Greenland, measured by number of visits to health clinic for 2 years after randomization, assessed by investigating medical records.

The null hypothesis is:There is no difference in the number of visits to health clinics for children with chronic otitis media with effusion or recurrent otitis media treated with bilateral ventilation tubes, compared with children not treated with ventilation tubes.

### Design

We have designed an investigator-initiated, parallel-group, multicentre, randomized clinical superiority trial of bilateral ventilation tube insertion versus treatment as usual (no ventilation tube) in Greenlandic children with chronic otitis media with effusion or with recurrent acute otitis media.

The Consolidated Standards of Reporting Trials (CONSORT) flow chart for the trial is shown in Fig. 1 [25]. The Standard Protocol Items: Recommendations for Interventional Trials (SPIRIT) participant timeline is given in Table 1 and the SPIRIT checklist is given in Additional file 1 [26].

**Fig. 1 Fig1:**
[figure not shown]
Consolidated Standards of Reporting Trials (CONSORT) trial flow chart

**Table 1 Tab1:** Participant timeline, Standard Protocol Items: Recommendations for Interventional Trials (SPIRIT) diagram

	Study period					
Time point	Enrolment	Allocation				Close-out
Enrolment:	−*t* _1_	0	*t* _1_	*t* _1_ + 3 months	*t* _1_ + 1 year	*t* _1_ + 2 years
Eligibility screen	X					
Informed consent	X					
Allocation	X					
Interventions:		X				
Ventilation tube insertion			X		X	
No ventilation tube insertion			X		X	
Assessments:						
Sex, age, ethnicity, socioeconomic factors	X					
Number of visits to health clinic						X
Questionnaires: Otitis Media-6 and Caregiver impact		X	X	X	X	X
Safety variables						X

We will consider all patients followed at a participating trial site for participation and include patients if they comply with the inclusion and exclusion criteria listed in Table 2.

**Table 2 Tab2:** Inclusion and exclusion criteria

Inclusion criteria	Exclusion criteria
Children aged 9–36 months	Children with orofacial cleft
Children with at least one Greenlandic born parent and at least one Greenlandic born grandparent	Children with Down’s syndrome
American Society of Anaesthesiologists’ physical status classification class 1 and 2	Children with known generalized immune deficiency
B-type curve, defined as flat line tympanograms or gradient <0.04 ml, or C2-type curve, defined as pressure ≤ −200 dPa, measured by tympanometry at two visits three-four months apart or	Children formerly treated with ventilation tubes
three episodes of acute otitis media in 6 months according to medical charts or	Lack of signed informed consent, signed by the legal guardian
tour episodes of acute otitis media in 12 months according to medical charts	
Signed informed consent, signed by the legal guardian	

The inclusion procedure is shown in Fig. 2.

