### Statistical plan and data analysis

Based on power (1 − *β*) = 0.80, *α* = 0.05 (two-sided) and standard deviation of five visits to health clinics andAn estimated eight visits to health clinics during 2 years in the control group andAn estimated six visits to health clinics during 2 years in the experimental group

we need a sample size of 99 individuals in each intervention group.

As we do not expect that data are normally distributed, the non-parametric van Elteren test will be used; thus, we obtain 99/0.86 = 115 participants per intervention group or 230 participants in total [34].

The two interventions will be compared regarding all outcomes. The analysis of the outcomes will be based on the intention-to-treat principle, i.e., all randomized participants will be included in the analysis, regardless of how much treatment they have received. Per-protocol analysis may be considered if important deviations from the protocol compromise the validity of the intention-to-treat analysis.

Dichotomous outcomes will be analyzed using logistic regression, continuous outcomes will be analyzed using linear regression and count data will be analyzed using the van Elteren test [34]. Our primary analysis will be adjusted for the stratification variables used in the randomization (trial site and type of otitis media). In secondary analysis, we will adjust all analyses (except when non-parametric tests are used) for additional significant design variables (age, sex, attending daycare, smokers in the household, diet, family history of otitis media). The statistical analysis will be described in detail in a separate paper published before the analysis of the trial results begins.

If only data are missing on the dependent outcome, we will use per-protocol data but we will interpret out results with caution if these missing data potentially bias our results. Otherwise, if more than 5% of the outcome data are missing, multiple imputation will be used (STATA 14). However, the 5% cut-off is not definitive. The imputation result will be considered the primary overall result. This analysis will be supplemented by the following sensitivity analyses:
**‘Best-worst-case’ scenario:** It will be assumed that all participants lost to follow-up in the experimental group have a mean score +2 standard deviations and have no event; and all those with missing outcomes in the control group have a mean score of −2 standard deviations and have an event.

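### A cheap gain in precision is left unused: no stated schedule or analysis takes the child's clinic-visit count before randomization as a baseline for the primary outcome

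*Protocol article*

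**What the plan says.** In Table 1 (Protocol article, Design) the row "Number of visits to health clinic" has a single mark, in the close-out column. The quality-of-life questionnaires, a secondary outcome, are also marked at allocation, so the schedule gives that outcome a baseline but gives the primary outcome none. The Primary outcome measure section counts visits only over the two years following randomization, from medical records read by blinded assessors.

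Under Statistical plan and data analysis, counts are compared by the van Elteren test and the primary analysis is adjusted for trial site and otitis type. Secondary analyses add "additional significant design variables (age, sex, attending daycare, smokers in the household, diet, family history of otitis media", but not where a non-parametric test is used. The visit count therefore gets no covariate beyond the strata. A separate statistical paper is promised before analysis begins.

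Table 2 shows that some chart history is already read at entry: one criterion is "three episodes of acute otitis media in 6 months according to medical charts", and another uses a 12-month look-back. The effusion route rests on tympanometry at two visits instead.

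**The concern.** How often a child attended a clinic before entry plausibly predicts how often the child attends afterwards. If so, leaving the earlier count out keeps explainable differences between children in the error term of the primary comparison. A chance imbalance in prior attendance between the arms would also go unseen. That matters for reading the result, because parents know the allocation.

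Precision is not plentiful here. The article describes a small population and reports six children randomized between 18 February and the end of June. It expects some drop-out, but the sample-size calculation contains no allowance for it. A baseline taken from existing records is one of the few ways to gain information without recruiting more children.

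**Working it through.** **Inputs from the Statistical plan section.** The plan gives "0.05 (two-sided) and standard deviation of five visits to health clinics", power 0.80, an "estimated eight visits to health clinics during 2 years in the control group" and an "estimated six visits to health clinics during 2 years in the experimental group", and a divisor of 0.86 for the rank test. The correlation r between earlier and later counts is not in the document. It is an assumption here, and should be read as the correlation left within the site and otitis-type strata.

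**The plan's own figure.** n per group = 2 × [5 × (1.960 + 0.842) / 2]² = 98.1, rounded up to 99. This agrees with the plan: "we need a sample size of 99 individuals in each intervention group". Then 99 / 0.86 = 115.1, stated as 115 per group and 230 in total. Strict rounding up would give 116 and 232. The figure reproduces.

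**Adding a baseline covariate on the same basis.** The residual SD is 5 × √(1 − r²). At 115 per group the effective n is 115 × 0.86 = 98.9, and power = Φ(2 / [SD × √(2/98.9)] − 1.96). At r = 0 this is Φ(2.813 − 1.96) = 80.3%.

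| Assumed r | 1 − r² | Power at 230 | Total N for 80% power (rounded up) |
|---|---|---|---|
| 0 | 1.00 | 80.3% | 232 |
| 0.2 | 0.96 | 81.9% | 222 |
| 0.3 | 0.91 | 83.9% | 210 |
| 0.4 | 0.84 | 86.6% | 194 |
| 0.5 | 0.75 | 90.1% | 174 |

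**How large could r be?** A mean of 8 with SD 5 gives variance 25 against 8 for a Poisson count, an excess of 17. Suppose all of that excess were a stable tendency of the child to attend. The squared coefficient of variation of that tendency is then 17/64 = 0.266.

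- 6-month window (mean 2): variance 2 + 4 × 0.266 = 3.06; covariance 8 × 2 × 0.266 = 4.25; r = 4.25 / √(25 × 3.06) = 0.49.
- 12-month window (mean 4): variance 8.25; covariance 8.5; r = 8.5 / √(25 × 8.25) = 0.59.

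These are upper-end values, before any selection at entry. If only half of the excess is stable, the covariance halves and r is about 0.24 or 0.30.

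**Simulation check.** Negative binomial counts with means 8 and 6 and 230 children were compared by a rank test, with and without covariance adjustment for the ranked earlier count.

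- Fully stable tendency: about 89% to 94% (6 months), and about 89–90% to 96% (12 months).
- Half stable: 88% to 88–90% (6 months), and 88–89% to 90% (12 months).
- Fully stable, but entry restricted to at least 3 visits in 6 months or 4 in 12 months: 96% to 97%, and 96% to 98%.

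Type I error of the adjusted test stayed near 5%. Unadjusted power starts above 80% because, in this model, the experimental arm has variance 6 + 36 × 0.266 = 15.6 (SD 3.9, not 5), and because the rank test does not lose the 14% efficiency that the plan allows for. The increments are the useful result, not the levels.

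**The case against.** The strongest reply is that nothing stated is wrong. Leaving a prognostic covariate out of a stratified randomized comparison neither biases it nor disturbs its type I error, and 99, 115 and 230 all reproduce. This stands, and it sets the limit of the point.

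A reader might infer from Table 1 that earlier visits are never collected, or that the information is lost. The document does not support that. Table 1 also leaves out daycare, household smoking, diet and family history, which the analysis intends to use, so absence from it does not prove non-collection. The visits also remain in the records and can be counted later. What can be said is that no stated schedule or analysis uses them.

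A reader might also take the planning values of mean 8 and SD 5 as proof that attendance is a stable trait, or take earlier visits to be the best available predictor. Neither follows. The excess variance could come from several contacts per illness or from short-lived disease, and the document gives no correlation. Selection on previous episodes narrows the range further. Otitis type, already a stratum, carries part of the prior history, and charts are the stated source of eligibility only for the recurrent acute route.

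Finally, collecting the count would not by itself change a plain van Elteren test, which takes strata and not a continuous covariate. That is correct, so the analysis must change with the data collection.

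**Conclusion.** The point holds as a modest, inexpensive improvement, not as an error. For an assumed r of 0.2 to 0.5, power at 230 on the plan's own basis moves from 80% to about 82–90%. If attendance is only weakly stable, or if entry criteria restrict the range, the simulations put the gain at 0 to 2 percentage points. The size rests wholly on a correlation that the document does not give.

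The point does not rest on silence about details left to the later statistical paper. The article itself limits the primary adjustment to the two stratification variables and exempts non-parametric tests from anything further.

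**What to change.** Add one field to the record-review form, and one mark to Table 1 before allocation: the number of health-clinic visits in a fixed window before randomization that every child has lived through. Six months would serve, since all children are at least 9 months old. A 12-month window would not be complete for those aged 9–11 months. Apply the same counting rule as for the outcome.

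In the promised statistical paper, before outcome data are analysed, pre-specify a stratum-wise rank-based test of the visit count with covariance adjustment for the ranked baseline count. Report the plain van Elteren test alongside it.

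The costs are small. Assessors read 6 further months on top of 24, a quarter more chart time per child (6/24 = 25%). Blinding is not threatened by the added months, because children with earlier tubes are excluded. The primary test does gain a covariate after randomization has begun, so the change should be dated and explained. The covariate itself is fixed before allocation and can be taken retrospectively for children already enrolled.

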**Fig. 2 Fig2:**
[figure not shown]
Inclusion procedure flowchart. AOM, acute otitis media; ENT, ear, nose and throat; OME, otitis media with effusion

We will include children aged 9–36 months. Infants younger than this age group require special anaesthesiological care, which cannot be offered in Greenland for ventilation tube insertion. The upper age limit has been set as low as possible in order to intervene before progression of the disease, while ensuring adequate sample size in this small population. We have attempted to reduce the number of exclusion criteria to as few as possible. However, children with orofacial cleft, Down’s syndrome and immune deficiency are, for other reasons, known to be at very high risk of chronic otitis media with effusion and recurrent acute otitis media and are therefore not comparable with other children. Children already treated with ventilation tubes can also not be included.

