### Interventions

The experimental intervention consists of bilateral insertion of ventilation tubes (Donaldson) in the tympanic membranes, administered under general anaesthesia.

Short-term ventilation tubes will be used, consistent with the tube type applied in the majority of other studies, and in accordance with the type that is expected to be introduced in Greenland [18, 23]. If the tympanic membrane is infected at the time of ventilation tube insertion, topical antibiotics will be given (Cilodex® [dexamethasone + ciprofloxacin] eardrop suspension, 3 mg + 1 mg, dexamethasone + ciprofloxacin) at a dose of four drops twice daily for 5 days.

If children in the intervention group seek medical assistance for ear problems after the insertion of ventilation tubes, these ear problems will be treated according to current practice in Greenland, which includes systemic antibiotic treatment (amoxicillin 40–90 mg/(kg day)), as well as aural toilette and topical antibiotics (ciprofloxacin 1 ml/3 mg, three drops, twice daily, or Cilodex® [dexamethasone + ciprofloxacin] eardrop suspension, 3 mg + 1 mg, four drops twice daily for 5–7 days).

The control intervention will be based on the current practice in Greenland, which includes systemic antibiotic treatment (amoxicillin, 40–90 mg(kg day)), as well as aural toilette and topical antibiotics (ciprofloxacin 1 ml/3 mg, three drops, twice daily). Children in the control group will not be offered ventilation tubes for any circumstance until at least 2 years after the first ENT visit and randomization.

Children in both the intervention group and control group will have an ENT examination, including otoscopy by an ENT specialist at least once a year and at the end of the study period, 2 years after randomization.

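### The 2-year perforation outcome takes no account of drums already perforated at entry, so it can mix existing with new perforations and dilute the relative effect

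*Protocol article*

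**What the plan says.** **Eligibility.** The Design section says the trial will "include patients if they comply with the inclusion and exclusion criteria listed in Table 2". One entry route in Table 2 is tympanometric, at two visits three to four months apart: "B-type curve, defined as flat line tympanograms or gradient <0.04 ml, or C2-type curve, defined as pressure ≤ −200 dPa". The other two are chart counts of acute otitis media, for example "three episodes of acute otitis media in 6 months according to medical charts or". The exclusions are orofacial cleft, Down's syndrome, known generalized immune deficiency, earlier ventilation tubes and lack of consent. Neither perforation nor chronic suppurative otitis media is listed. The text under Fig. 2 presents the short list as deliberate: "We have attempted to reduce the number of exclusion criteria to as few as possible".

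**Outcome.** Under Secondary outcome measures, the fourth item is the share of children in each arm with a perforation in one or both drums at 2 years, read from anonymized otoscopic photographs. It is not limited to new perforations, and it makes no reference to the state of the drum at entry.

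**Analysis.** The statistical section assigns dichotomous outcomes to logistic regression. The primary analysis adjusts for trial site and type of otitis media. The secondary analysis adds age, sex, daycare, household smoking, diet and family history. Drum status at entry is in neither list.

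**Epidemiology and aim.** The Background places the peak hazard in the second half of the first year of life. Its sentence, cut here before the upper bound of 12 months, begins: "The cumulative incidence of chronic suppurative otitis media in Greenland is 14% at the age of 4, with the highest hazard rate between 6 and". It gives a prevalence of chronic suppurative otitis media of 9% to 14% in Nuuk and Sisimiut, both of which are trial sites. It argues for early intervention so that fewer children go on to chronic perforation. On age at entry, the text under Fig. 2 says: "The upper age limit has been set as low as possible in order to intervene before progression of the disease".

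**The concern.** The trial's interest in perforation is about progression: whether tubes prevent a chronic perforation from forming. A drum already perforated when the child is randomized cannot show that benefit. If it is still perforated at 2 years, it nevertheless counts as an event in whichever arm the child was assigned to.

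The written entry rule lets such children in. The chart routes ask nothing about the drum. The tympanometric route accepts any flat line without requiring an intact drum. That a perforated drum can also give a flat trace is general measurement knowledge and is not stated in the article, but the chart routes leave the gap open without it.

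Because the peak hazard falls before or at the start of the 9 to 36 month entry window, the document's own figures make some perforations before entry plausible. The measured outcome would then be a mixture of existing and new perforations. A real preventive effect would look smaller on the relative scale and be harder to detect.

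**Working it through.** **The plan's own figure.** The article gives no sample size or expected rate for the perforation outcome. Its only calculation is for visits: 2 × (1.96 + 0.8416)² × 5² / 2² = 98.1, rounded up to 99 per arm, and 99 / 0.86 = 115.1, taken as 115 per arm and 230 in total. This reproduces and the present point does not affect it. It is used here only to supply 115 per arm.

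**Inputs for the illustration (assumptions, not document figures for this sample).**
- q: share of children perforated at entry and still perforated at 2 years, equal in both arms. Values of 0, 5%, 10% and 14% are used. The article does not give the entry share; the range is set with its general 9% to 14% prevalence in view.
- New perforations over 2 years among children with intact drums: 14% in controls and 7% with tubes, a true risk ratio of 0.50.

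**Formula.** Observed proportion at 2 years = q + (1 − q) × new-perforation risk.

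- q = 10%, control: 0.10 + 0.90 × 0.14 = 0.226
- q = 10%, tubes: 0.10 + 0.90 × 0.07 = 0.163
- Risk ratio: 0.163 / 0.226 = 0.72

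| q | Children per arm (115 × q) | Control | Tubes | Risk ratio | Difference (points) | Existing perforations as share of control events (q / control) |
|---|---|---|---|---|---|---|
| 0 | 0 | 14.0% | 7.0% | 0.50 | 7.0 | 0% |
| 5% | 5.8 | 18.3% | 11.7% | 0.64 | 6.65 | 27% |
| 10% | 11.5 | 22.6% | 16.3% | 0.72 | 6.3 | 44% |
| 14% | 16.1 | 26.0% | 20.0% | 0.77 | 6.0 | 54% |

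**Precision.** With a two-sided 5% normal-approximation test of two proportions at 115 per arm, power for these pairs is 41%, 29%, 23% and 19%. Restricting to children intact at entry leaves 115 × (1 − q) per arm, that is 109, 104 and 99 for q of 5%, 10% and 14%. The comparison is again 14% versus 7%, and power is 39%, 38% and 36%. Under these assumptions, restriction recovers most of the loss despite the smaller denominator.

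**Healing.** Only persistent perforations enter q. If 10% were perforated at entry and half healed, the 5% row would apply, provided healed drums then carry the same risk of a new perforation as intact ones.

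**The case against.** **The article is condensed and Fig. 2 is not shown.** An ear, nose and throat specialist enrols the children, so drum status may well be looked at and even recorded. That stands as a limit on what can be said about entry practice. It does not settle the point: the text makes Table 2 the rule, and the outcome definition and the named adjustment variables make no use of drum status even if it is recorded.

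**The target condition narrows the gap.** Chronic otitis media with effusion is defined in the Background as fluid in the middle ear, which a dry open ear would not meet, and a C2 curve implies a closed drum. The point therefore concerns flat curves and the chart-based routes.

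**Allocation is randomized.** A reader might infer that the perforation comparison is biased. It is not, because existing perforations are balanced in expectation. What remains is dilution on the relative scale, lost precision and chance imbalance.

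**The size depends on assumptions.** The 9% to 14% prevalence has no stated age, the 14% cumulative incidence runs to age 4, and using 14% both for entry and for new events is generous. The absolute difference moves only from 7.0 to 6.0 points. The outcome is also secondary, the sample was not sized for it, and in this illustration power is 41% at best. All of this stands and is why the figures are only an illustration.

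**Broad entry is a declared choice.** A reader might infer that perforated children must be excluded. The documents do not support that: exclusions were kept few in a small population, and the outcome can be repaired without removing anyone from the trial.

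**Conclusion.** The point holds for the perforation outcome. Table 2 does not bar an existing perforation, the outcome counts any perforation at 2 years, and the analysis does not allow for entry status. Children already perforated are therefore eligible to be randomized, and their persistent perforations are eligible to be counted as events. The article does not show that this has happened or how often it would.

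Under the stated assumptions (new perforations 14% versus 7%, full persistence, equal entry share in the arms), a true risk ratio of 0.50 would be observed as about 0.64, 0.72 or 0.77 at entry shares of 5%, 10% or 14%. A lower entry share or healing would shrink this.

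A reader might go further and infer a loss of power for the primary outcome, on the ground that the plan tubes both ears ("The experimental intervention consists of bilateral insertion of ventilation tubes (Donaldson) in the tympanic membranes, administered under general anaesthesia") and a tube could add little in an open ear. The documents do not support that. They say nothing about the effect of tubes on visits in perforated children, a child with one perforated ear still has another ear at risk, and the two-visit difference is an average for the enrolled population.

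**What to change.** 1. At the enrolling specialist's examination, record before randomization whether each drum is intact or perforated.
2. Define the fourth secondary outcome as perforation at 2 years among children, or ears, with an intact drum at entry. Entry status is fixed before allocation, so this restriction keeps the randomized comparison. If ears are the unit, allow for two ears in one child.
3. Alternatively, keep all children and add entry drum status to the logistic regression for this outcome. If nearly all existing perforations persist, this gives almost the same result as restriction.
4. Report the number perforated at entry in each arm.

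**Cost.** One case report form item and one line in the outcome definition or model, plus a slightly smaller denominator if the analysis is restricted (in the illustration, 99 to 109 instead of 115 per arm). Six children had been randomized by the end of June, so a change made at about that time would cover nearly the whole sample. Drum status that was not recorded at entry cannot be recovered by a later analysis plan.
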